Therefore, only studies of people who vape but have never smoked CCs or have only a limited smoking history (ie, those who have smoked fewer than 100 CCs in their lifetime) can enable the detection of harms attributable to EC use. Without studies of people who use ECs with no established smoking history, it will be impossible to distinguish the harms of vaping from neither vaping nor smoking. Concluding that vaping poses less risk than smoking is easy [11,15-20,27-29]. Quantifying the absolute health risks of vaping independent of smoking requires cleaner data.

In a small study of daily EC users who had never smoked, no noticeable changes in blood pressure, heart rate, lung function, respiratory symptoms, exhaled breath nitric oxide, exhaled carbon monoxide, and high-resolution computed tomography of the lungs from baseline were observed over an average 3.5-year observation period [30]. Daily exposure to EC aerosol emissions caused no significant changes in any of the health outcomes investigated, including measures of lung function and lung inflammation. Moreover, no significant structural abnormalities were identified in the high-resolution computed tomography of the lungs, and no respiratory symptoms were consistently reported. Some of the strengths of this study included prospective rather than retrospective data collection from study participants; the detailed vaping history and precise characterization of the study participants; as well as the use of a panel of different clinical, functional, and inflammatory measures during the study.

Large prospective studies of well-characterized EC users with and without a history of CC smoking are warranted to establish the long-term effects of regular vaping on respiratory health. We will conduct a global cross-sectional survey of individuals from 6 world regions. Respiratory symptoms reported by a cohort of individuals who vape with no established history of CC smoking or other tobacco or nicotine product use will be compared against those reported by a cohort of matched controls with no established history of vaping, smoking, or use of any other tobacco products.

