### Recruitment

Carefully selected recruiters, the VERITAS (Vaping Effects: Real-World International Surveillance) ambassadors (AB, [name], AM, KY, and MS), will make sure to identify and screen individuals for the VERITAS Cohort Study. The VERITAS ambassadors will pursue recruitment through social media channels, WhatsApp groups, Google email groups, posters in vape shops and universities, recommendations from other participants, and recommendations from local vape shop owners in each of the 6 geopolitical world regions (ie, Africa and Middle East, North America, Latin and South America, Asia-Pacific, Western Europe, and Eastern Europe). Ambassadors will instruct vape shop owners to ask their regular clients about their smoking history and EC use patterns to identify potential participants. The reference or control group will comprise adults who never used any tobacco or nicotine products. Control group participants will be recruited primarily among vaping individuals’ circles of friends and acquaintances. They will be matched for age and sex to the extent possible. In the event of shortfalls from this recruiting pathway, the Veritas Ambassadors will recruit further controls.

VERITAS ambassadors will be acting as the main point of contact for study participants and will be coordinated by a project leader ([name]). A document detailing the ambassadors’ roles can be found on the VERITAS Cohort website [33].

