#### Inclusion Criteria

Eligibility for participation in the study is determined by the following criteria. All individuals who wish to participate must be aged ≥18 years and provide informed consent to participate in the study.

The vapers cohort should meet the following inclusion criteria:

Use at least 1 of 3 types of EC or vape—disposables, rechargeable with replaceable prefilled pods or cartridges, or rechargeable and refillable with e-liquid.Have never smoked a CC *or* have smoked a CC *but* have not smoked more than 100 CCs in their lifetime [34] *and* have not smoked a CC in the past 3 months.Has never used, *or* has never used more than once a week, any of 9 other tobacco or nicotine products listed below:Traditional cigarsCigarillos or filtered cigarsSmoked tobacco in a hookahSmoked tobacco in a pipeSmokeless tobacco (including dip, spit, moist snuff, pouches, and chewing tobacco)Snus pouchesDissolvable tobaccoHeated tobacco products (eg, iQOS, Glo, and Pulze)Tobacco-free nicotine pouches

The controls cohort should meet the following inclusion criteria:

Have never used, or have never used more than once a week, any of the 3 types of EC or vaping products listed above.Same as the vapers cohort’s inclusion criterion 2.Same as the vapers cohort’s inclusion criterion 3.

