#### Exclusion Criteria

Individuals who do not satisfy the criteria for inclusion in either the vapers cohort or the controls cohort will be excluded.

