### Study End Points

The primary end point of the study is the RSES score [35]. The objective of the study is to compare the RSES scores between people who vape with no established CC smoking history (ie, the “vapers cohort”) and people who have never vaped nor smoked (ie, the “controls cohort”).

Additionally, the study will collect data to carefully characterize people who vape with no established CC smoking history in the “vapers cohort.” Data collection will include information about the age of initiation of using vaping products, reasons for starting and continuing use of vaping products, specific types of products used, flavors and nicotine strengths of recently used vaping products, as well as the frequency and intensity of product use in the past 30 days.

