### Statistical Analyses and Reporting

The primary objective of the study is to retrospectively estimate the effect of current, regular use of vaping products on respiratory symptom experience in the past 30 days, measured in this study by the mean score (0 to 5) on the 5-item RSES [35]. Details of sample size calculation and power analysis to detect differences in respiratory symptoms (ie, the RSES scores) between the “vapers cohort” and the “controls cohort” are included in Multimedia Appendix 1. In brief, with 75 participants per group, a study should be adequately powered to detect a difference of 0.57, the proposed minimal important difference, with a power of 98%. However, to detect a more conservative difference of 0.40, a study with 75 individuals per group would still have a power of 89%. The target study population will consist of approximately 500 exposed individuals and 250 matched controls–approximately 83 people who vape per each of the 6 world regions. If the initial recruitment falls short of the goal, or in the case of substantial early loss to follow-up, rolling enrollment will be considered to make up the deficit.

Data analysis of the RSES scores will be both descriptive and inferential in nature. The RSES scores and the demographic characteristics of the vapers cohort and the controls cohort will be descriptively summarized. We will test the null hypothesis that the RSES scores will not significantly differ between the vapers cohort and the controls cohort when adjusted for demographic differences. This hypothesis will be tested through a one-way between-subjects Analysis of Covariance in which the mean RSES score will be entered as the dependent variable, “Cohort” will be entered as the between-subjects independent variable, and 4 demographic variables—age, sex, education, and employment status—will be entered as covariates. Inferential and descriptive statistics will be reported for the Cohort variable adjusted for the effects of the covariates. *P* values <.05 will be considered statistically significant.

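### Controls may vape up to once a week although the end point compares vapers with never-vapers, and a current light vaper meets both cohorts' criteria with no rule to place them

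*Protocol article*

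**What the plan says.** The article describes the control group in several ways.

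- Inclusion Criteria, the operative rule: controls "Have never used, or have never used more than once a week, any of the 3 types of EC or vaping products". On smoking the rule is "Same as the vapers cohort’s inclusion criterion 2", and other tobacco and nicotine products are handled the same way. Controls may thus have smoked up to 100 cigarettes in their lifetime (none in the past 3 months) and used the nine other products up to weekly.
- Study End Points: controls are "people who have never vaped nor smoked".
- Recruitment: "The reference or control group will comprise adults who never used any tobacco or nicotine products".
- Introduction, more loosely: "matched controls with no established history of vaping, smoking, or use of any other tobacco products".

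For the vapers cohort, the first criterion is "Use at least 1 of 3 types of EC or vape", with no frequency. Statistical Analyses and Reporting states the aim as to "retrospectively estimate the effect of current, regular use of vaping products on respiratory symptom experience in the past 30 days".

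Exclusion Criteria says: "Individuals who do not satisfy the criteria for inclusion in either the vapers cohort or the controls cohort will be excluded". Web-Based Survey Questionnaires says that cohort membership follows from the survey answers on past and current product use.

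**The concern.** The primary analysis rests on one contrast, and its reference group is defined in incompatible ways. An occasional vaper is an eligible control under Inclusion Criteria and is not a control at all under Study End Points or Recruitment. The vapers criterion does not enforce the regular use that the objective names, so the same occasional vaper also qualifies as exposed.

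The direction matters because the study's hypothesis is that vaping causes no increase in symptoms, and it is examined with an ordinary difference test. Exposed people among controls, or barely exposed people among vapers, make a non-significant result easier to obtain. The error would lean toward the result the study expects.

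**Working it through.** **1. Can one person meet both sets?** Take someone who now vapes once a week or less, has never vaped more often, and meets the smoking and other-product limits.

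- Vapers criterion 1 is met: the person uses at least one product type.
- Controls criterion 1 is met: the person has never used more than once a week.
- Criteria 2 and 3 are identical in both cohorts, so they cannot separate the two.
- Exclusion Criteria removes only people who fit neither cohort.
- Web-Based Survey Questionnaires says assignment uses the survey answers, but gives no rule for someone who fits both.

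The overlap is therefore real as written.

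**2. The plan's own power figures.** The article states 98% power for 0.57 and 89% for 0.40, with 75 per group, and gives no SD. With power = Φ(d / [SD·√(1/n₁ + 1/n₂)] − 1.96), two-sided 5% assumed, the implied SDs are 0.870 and 0.769. A common SD between 0.743 and 0.793 returns both figures within 2 points; SD 0.77 gives 99.5% and 88.9%. Because the SD is back-solved, this is not an independent reproduction, but nothing shows the stated power to be wrong. SD 0.77 is used below.

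**3. Attenuation.** Let d be the true difference between regular vapers and never-vapers, c and v the shares of light vapers among controls and vapers, and f the fraction of the regular-use effect that light vapers carry. Then

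observed difference = d·[(1 − v) + v·f − c·f].

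The documents give none of c, v or f; all are assumed. For d = 0.57:

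| Share of light vapers | Controls only, f = 1 | Controls only, f = 0.5 | Same share in both cohorts, any f |
|---|---|---|---|
| 10% | 0.57 × 0.90 = 0.51 | 0.57 × 0.95 = 0.54 | 0.51 |
| 20% | 0.57 × 0.80 = 0.46 | 0.57 × 0.90 = 0.51 | 0.46 |
| 30% | 0.57 × 0.70 = 0.40 | 0.57 × 0.85 = 0.48 | 0.40 |

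With c = v the formula reduces to d·(1 − c), so f cancels. With light vapers among controls only and f = 0, there is no attenuation.

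**4. Effect on power at 500 and 250.** SE = 0.77 × √(1/500 + 1/250) = 0.0596.

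- True 0.40 cut by 30% to 0.28: 0.28/0.0596 − 1.96 = 2.73, power 99.7%. At SD 0.87 it is 98.6%.
- An assumed smaller true difference of 0.20: power 91.8% without attenuation, and 85.5%, 76.5% and 65.1% when it is cut by 10%, 20% and 30%.

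**5. Price of exclusive cohorts.** If 20% of both cohorts are dropped (assumed), 500 and 250 become 400 and 200, and the confidence interval widens by √(1/0.8) = 1.118.

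**The case against.** The best defence is that the intended split is visible. The objective names regular use, the survey dates initiation from vaping more than once a week, the control criterion uses the same cut-point, and the Introduction speaks of no established history. On this reading the frequency floor was simply left out of the vapers criterion. The survey's routing is not shown and may contain the missing rule. This has force: the overlap may be only a drafting gap. It does not remove the conflict between Inclusion Criteria and the two sections that say never, nor does it take occasional vapers out of the controls.

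Some stronger readings are tempting, and the documents do not support them.

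- A reader might infer that staff can choose the cohort for a light vaper. The article says assignment follows from survey answers.
- A reader might infer that occasional vaping among controls is likely, because they come mainly from vapers' social circles. No prevalence is given, and the same section says these controls never used such products.
- A reader might count the smoking and other-product allowances as further dilution. They conflict with the never wording, but they apply equally to both cohorts and are not a source of the attenuation described here.

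**Conclusion.** The point holds as a contradiction in the definition of the reference group, together with a gap in cohort assignment. It should be settled before scores are compared.

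The direction of bias is toward no difference, provided that regular vaping raises symptoms and occasional vaping raises them no more. Its size cannot be derived from the article. It is zero if no light vapers enrolled or if vaping has no effect; under the assumed 10–30% shares among controls only, it is 10–30% at full effect and 5–15% at half effect.

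It might be inferred that the study could no longer detect its stated differences. That does not follow: even the largest attenuation shown leaves power for 0.40 near 99% or above at the target size, under an SD back-solved from the plan's own figures. What is lost is accuracy of the estimate and sensitivity to smaller differences.

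**What to change.** Enrolment is reported complete, so this is a change to the analysis-set definition and wording, to be fixed before the cohorts' scores are compared.

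- Controls in the primary analysis: people who have never vaped, as Study End Points states.
- Vapers in the primary analysis: people currently vaping more than once a week, the threshold already used in Inclusion Criteria and in the survey.
- People who vape, or have vaped, only once a week or less: in neither cohort.
- Sensitivity analysis: the cohorts as recruited.
- Wording: give the same control definition in Recruitment, Inclusion Criteria and Study End Points. Describe the smoking and other-product limits as the same no-established-use limits in both cohorts, not as never-use.

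Derive these sets from the past and current use answers collected for cohort assignment, and confirm in the survey document that they suffice. A control definition based on no vaping in the past 30 days is less safe, because the article describes the 30-day use items only for the vapers cohort.

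The cost is that some participants leave the primary comparison. Their number is unknown; at an assumed 20% of both cohorts, the interval is about 12% wider. For an assumed true difference of 0.20 and SD 0.77, power at 400 and 200 would be Φ(0.20/[0.77 × √(1/400 + 1/200)] − 1.96) = Φ(1.04), about 85%. That compares with 76.5% if a 20% share of light vapers stayed in both cohorts.

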#### Exclusion Criteria

Individuals who do not satisfy the criteria for inclusion in either the vapers cohort or the controls cohort will be excluded.

### Study Procedures

All study procedures, from recruitment and obtaining consent to eligibility checks, questionnaires, data collection, and participant compensation, will be carried out exclusively online. The VERITAS web-based survey software (custom-based) will serve as the primary platform for data collection and displaying the Informed Consent Form. This software is intended not only to optimize the presentation of materials for study participants but also to facilitate data submission across various devices, such as laptops, smartphones, and tablets, while being compatible with all web browsers, including Chrome, Safari, Firefox, and Internet Explorer. By adopting this approach, study participants will have the freedom to engage in the research at their convenience, within the privacy of their choosing, and using their preferred device. As a result, participants will be empowered to take part in the study on their terms, in a comfortable setting, and at a time that suits them best.

### Web-Based Survey Questionnaires

After prescreening by the ambassadors, eligible individuals who consent to participate will be directed to the study website [32], where they will be subject to a 2-step verification process. When participants reach the survey platform, they will click “Don’t have an account? Register”; participants will register their email addresses. Following registration, participants will receive a “Welcome email” and a link to re-enter the survey platform, where they will be asked for their phone number to receive a confirmation code via SMS. After confirming their email addresses, they will start filling out the survey, which will consist of sociodemographic data, medical history, as well as tobacco and nicotine product use behavior. Details about the VERITAS survey document can be shared upon specific request to the corresponding author. The information collected via the web-based questionnaire will help to characterize or describe the unique cohort. Individuals will then be included in the vapers cohort or the controls cohort or they will be excluded based on their responses to questions about their past and current use of cigarettes, EC or vapes, and other tobacco and nicotine-containing products.

Individuals in the vapers cohort will then be asked questions about their historical and current patterns of use of 3 types of vaping products (ie, disposable vaping products, rechargeable prefilled pod vaping products, and rechargeable refillable vaping products). For each vaping product category, data will be collected on 12 outcomes, as applicable: (1) age of first use; (2) age of initiation, when started to vape more than once a week; (3) the number of product units used in their lifetime; (4) the number of product use days in the past 30 days; (5) length of time (eg, years or months) of vaping more than once a week; (6) nicotine content of products used; (7) flavor categories vaped more than once a week; (8) number of flavors vaped more than once a week; (9) name of favorite flavor used in the past 30 days; (10) number of product units used in the past 30 days; (11) reasons for initiating product use (free-text response); and (12) reasons for current product use (free-text response). The VERITAS survey document can be shared upon specific request to the corresponding author.

All participants will then complete the Respiratory Symptom Experience Scale (RSES), a validated scale that asks participants to rate the frequency with which they experienced 5 respiratory symptoms in the past 30 days [35]. The 5 symptoms rated are as follows: (1) morning cough with phlegm or mucous, (2) coughing frequently throughout the day, (3) shortness of breath that makes it difficult to do normal daily activities, (4) becoming easily winded during normal daily activities, and (5) wheezing or whistling in the chest at times when not exercising or doing other physically strenuous daily activities. Rating for each symptom is made on a 5-point scale, where 1=Never (0 out of the last 30 days); 2=Rarely (1-5 days); 3=Occasionally (6-15 days); 4=Most days (16-29 days); 5=Every day (all 30 out of the last 30 days). A mean RSES score will be calculated by averaging the 5-item scores. The RSES can be found in the Multimedia Appendix 1.

Lastly, questions will assess participants’ sex, country of residence, employment status, highest educational attainment, height, and weight.

If necessary, surveys will be translated into the local language by the ambassador for countries where not all participants are fluent in English. Data will be collected on whether the participant completed the survey in English, Spanish (translation available on the platform), or their local language (in case it is determined that some questions of interest had some important difference in nuance when translated).

### Study End Points

The primary end point of the study is the RSES score [35]. The objective of the study is to compare the RSES scores between people who vape with no established CC smoking history (ie, the “vapers cohort”) and people who have never vaped nor smoked (ie, the “controls cohort”).

Additionally, the study will collect data to carefully characterize people who vape with no established CC smoking history in the “vapers cohort.” Data collection will include information about the age of initiation of using vaping products, reasons for starting and continuing use of vaping products, specific types of products used, flavors and nicotine strengths of recently used vaping products, as well as the frequency and intensity of product use in the past 30 days.

### Statistical Analyses and Reporting

The primary objective of the study is to retrospectively estimate the effect of current, regular use of vaping products on respiratory symptom experience in the past 30 days, measured in this study by the mean score (0 to 5) on the 5-item RSES [35]. Details of sample size calculation and power analysis to detect differences in respiratory symptoms (ie, the RSES scores) between the “vapers cohort” and the “controls cohort” are included in Multimedia Appendix 1. In brief, with 75 participants per group, a study should be adequately powered to detect a difference of 0.57, the proposed minimal important difference, with a power of 98%. However, to detect a more conservative difference of 0.40, a study with 75 individuals per group would still have a power of 89%. The target study population will consist of approximately 500 exposed individuals and 250 matched controls–approximately 83 people who vape per each of the 6 world regions. If the initial recruitment falls short of the goal, or in the case of substantial early loss to follow-up, rolling enrollment will be considered to make up the deficit.

Data analysis of the RSES scores will be both descriptive and inferential in nature. The RSES scores and the demographic characteristics of the vapers cohort and the controls cohort will be descriptively summarized. We will test the null hypothesis that the RSES scores will not significantly differ between the vapers cohort and the controls cohort when adjusted for demographic differences. This hypothesis will be tested through a one-way between-subjects Analysis of Covariance in which the mean RSES score will be entered as the dependent variable, “Cohort” will be entered as the between-subjects independent variable, and 4 demographic variables—age, sex, education, and employment status—will be entered as covariates. Inferential and descriptive statistics will be reported for the Cohort variable adjusted for the effects of the covariates. *P* values <.05 will be considered statistically significant.

The secondary objective of this study is to characterize the use of different vaping products by the vapers cohort. Data analysis of this objective will be purely descriptive in nature. Descriptive summary statistics will be reported for all questionnaire measures of vapers’ use of vaping products within each of the 3 product categories—disposable vapes, rechargeable prefilled pod vapes, and rechargeable refillable vapes. Data on the following variables will be descriptively summarized for the subsets of participants within the vapers cohort who are current users of each product category, as follows: number of current users, age of first use, age of first regular use, number of products used in a lifetime, number of product use days in the past 30 days, time of regular product use, the nicotine concentration of products used typically, type of e-liquid flavors used in the past 30 days, number of e-liquid flavors used regularly in the past 30 days, and number of products used in the past 30 days.

Descriptive summary statistics for continuous variables will include the number of participants in the population of interest (N), the number of participants in the population of interest with nonmissing data on the variable or measure (n), as well as appropriate measures of central tendency (eg, mean and median) and dispersion (eg, SD, SE, range, and IQR) for the observed data. Descriptive statistics reported for categorical variables or measures will include the total number of participants in each subject group who provided nonmissing responses, the proportion of each subject group who selected each categorical response option, and when appropriate, 95% CIs around the proportion of participants who selected each categorical response option.

Additional data analyses may be conducted where data on variables or measures are filtered or stratified by other independent variables of interest. If undertaken, the reporting of descriptive summary statistics for each variable or measure filtered and stratified by additional independent variables of interest will closely resemble the reporting of the planned analyses described above. All data analyses will be conducted using the IBM SPSS (version 27 or higher; IBM Corp) statistical software. Data tables not presented in primary reports or in the manuscript will be presented in supplementary files.

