The primary aim of this study is to test the hypothesis that chronic exposure to EC aerosols does not cause an increase in respiratory symptoms among people who vape with no established cigarette smoking or other tobacco and nicotine product use history. The secondary aims are to determine the feasibility of assembling a large cohort of individuals who vape with no other established tobacco or nicotine product use history to evaluate such effects for future studies and to characterize patterns of vaping product use behavior among this unique cohort.

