## Discussion

Research into the respiratory health effects of regular vaping is limited [11,36,37]. Previous research investigating the health status of individuals who used to smoke faces challenges due to unknown health effects caused by prior smoking. Consequently, studies involving individuals who solely vape with no established smoking history are essential to identify potential harms attributed to vaping. A small prospective study of daily EC users who never smoked CCs demonstrated no significant alterations in lung function, inflammation, or structural abnormalities observed in lung scans [30]. Moreover, consistent respiratory symptoms were not reported in this study [30]. However, large longitudinal studies focusing on well-characterized EC users, with and without a history of CC smoking, are necessary to establish the long-term effects of regular vaping on respiratory health.

This proposed study aims to be the first investigation exploring the association between respiratory health effects and the use of ECs in a large group of individuals who exclusively vape, with no established CC smoking history. Additionally, the research will delve into potential confounding factors that could influence any association identified between vaping and respiratory symptoms.

Several noteworthy features distinguish this study. First, by enlisting participants globally, it intends to capture diverse experiences and behaviors related to EC use across different countries and regions. Second, the study’s focus on respiratory symptoms and in-depth characterization of vaping product use in a real-world context enhances its generalizability. Third, the study sample has been adequately powered to detect minimum clinically important differences in respiratory symptoms between exclusive vapers and those who neither vape nor smoke. Finally, the study implements a stringent 2-step verification process to deter potential abuse by unauthorized users attempting to exploit the possibility of receiving a gift card and uses manual analysis to identify and verify legitimate participants.

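### The primary aim is a directional no-increase hypothesis, but the only decision rule is a non-directional difference test at P<.05 with no bound; aim and test need reconciling before analysis

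*Protocol article*

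**What the plan says.** The Introduction (aims) states the primary aim as to "test the hypothesis that chronic exposure to EC aerosols does not cause an increase in respiratory symptoms among people who vape" with no established history of other tobacco or nicotine use. This is directional and is a claim of absence.

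Statistical Analyses and Reporting turns it into: "We will test the null hypothesis that the RSES scores will not significantly differ between the vapers cohort and the controls cohort", after adjustment for demographic differences. "This hypothesis will be tested through a one-way between-subjects Analysis of Covariance" of the mean RSES score, with cohort as the factor and age, sex, education and employment status as covariates. The criterion is that P "values <.05 will be considered statistically significant". No margin and no confidence-limit criterion is stated.

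The same section uses two thresholds of size, both only for power with 75 per group: 98% power to "detect a difference of 0.57, the proposed minimal important difference", and 89% power for a more conservative 0.40. The Discussion lists it as a strength that the sample is "adequately powered to detect minimum clinically important differences in respiratory symptoms".

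The objective is also worded in two other ways. Study End Points speaks of comparing RSES scores between the cohorts, and Statistical Analyses and Reporting opens with retrospectively estimating the effect of current regular vaping. Neither has a direction or a threshold.

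**The concern.** The hypothesis the study hopes to support has been placed as the null of a difference test. Three things follow.

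- Failure to reject a null does not establish it. To support no increase, the data must exclude an increase of some stated size, and no size is stated in the rule.
- The cohort F test is non-directional. Fewer symptoms in vapers would reject the null without contradicting the aim.
- The plan has a yardstick for relevance (0.57, or 0.40) but leaves it out of the decision. A significant result therefore says nothing about whether an increase is large enough to matter.

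The null is also worded in terms of scores not differing significantly. That describes a test result and not the population means.

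At stake is the primary conclusion. The article fixes both the hypothesis and the test, and they do not match, so this is more than a detail left to an analysis plan.

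**Working it through.** **Inputs**

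- Statistical Analyses and Reporting: 75 per group, power 98% at 0.57 and 89% at 0.40; target 500 vapers and 250 controls; significance level .05. Sidedness is not stated, but the F test for a two-level factor is equivalent to a two-sided test.
- Results: 748 enrolled, split not given. I use 500/250.
- SD of the mean RSES score: not in the article, which refers to Multimedia Appendix 1 (not shown) for the sample-size details. It is an assumption here. I ignore any precision gained from the covariates.

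**Step 1. The plan's own power figures.** Power ≈ Φ(δ / (SD·√(2/75)) − 1.96).

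- 98% at 0.57 gives SD 0.87: 0.57 / (0.87 × 0.1633) = 4.01, and Φ(2.05) = 0.98.
- 89% at 0.40 gives SD 0.77: 0.40 / (0.77 × 0.1633) = 3.18, and Φ(1.22) = 0.89. The noncentral t gives 0.76.
- No single SD gives both figures exactly. Any SD from 0.745 to 0.79 comes within 2 percentage points of both, so I do not call either figure wrong.

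Working range: 0.76 to 0.87. Wider check: 0.4 to 1.0.

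**Step 2. Smallest significant difference at 500/250.** SE = SD·√(1/500 + 1/250) = SD × 0.0775; threshold = 1.96 × SE.

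| SD | SE | Threshold | Share of 0.57 |
|---|---|---|---|
| 0.76 | 0.059 | 0.115 | 20% |
| 0.87 | 0.067 | 0.132 | 23% |
| 0.4 | 0.031 | 0.061 | 11% |
| 1.0 | 0.077 | 0.152 | 27% |

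**Step 3. A small true increase.** Take a true difference of 0.20, about 35% of 0.57 (0.20/0.57). P(significant) ≈ Φ(0.20/SE − 1.96):

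- SD 0.76: Φ(3.40 − 1.96) = 92%.
- SD 0.87: Φ(2.97 − 1.96) = 84%.

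The chance that the upper 95% limit falls below 0.40 is Φ((0.40 − 0.20)/SE − 1.96), which gives the same 84% to 92%. In this situation the P<.05 rule would usually count against the no-increase hypothesis, while the interval would usually show the increase to be below 0.40.

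**Step 4. What a non-significant result would imply.** The estimate is then at most 1.96·SE, so the upper 95% limit is at most 2 × 1.96 × SE: 0.23 at SD 0.76, 0.26 at SD 0.87 and 0.30 at SD 1.0. All are below 0.40.

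**Step 5. Power of a bound-based rule at a true difference of 0.** Power = Φ(margin/SE − 1.96).

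- Margin 0.40, SD 0.87: Φ(5.94 − 1.96) > 99.9%; higher still at SD 0.76.
- Margin 0.20: 84% (SD 0.87) to 92% (SD 0.76).

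**The case against.** The strongest reply has four parts.

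1. The no-increase sentence is only one of three statements of the objective. For comparing or estimating, an adjusted difference with a significance test is a reasonable analysis. This stands. The defect is that the statements disagree, and rewording the aim is as valid a repair as adding a margin.

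2. A reader might infer that neither possible result answers the aim. The documents do not support that. The Introduction says no increase, not no clinically important increase, so a significantly higher score in vapers does bear against the literal hypothesis, subject to confounding. Significance at 0.12 to 0.13 makes the test uninformative about relevance; it does not make it invalid.

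3. A reader might also infer that a non-significant result would leave a large increase open. At the planned size it would not: step 4 puts the upper limit below both 0.40 and 0.57. The adjusted cohort results are to be reported, so the limit should be recoverable, although an interval for this comparison is not explicitly promised. This limits the practical damage. It does not replace a bound chosen in advance.

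4. Nothing in the article says that a non-significant result will be reported as proof of no increase, and the Discussion limits causal conclusions because of the cross-sectional design. Such reporting is a risk of how the hypothesis is set up, not a stated plan.

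It is also fair that 0.57 should not simply be adopted as a margin. It is the whole proposed minimal important difference, and the article offers it only as a difference to detect.

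**Conclusion.** The mismatch is real. The aim is directional and claims absence, while the only rule is a non-directional P<.05 test of no difference with no bound. As written, a non-significant result does not establish the aim, and a significant one does not separate a trivial from an important increase.

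The threshold for significance is about 0.12 to 0.13, roughly one fifth of 0.57. This rests on an SD of 0.76 to 0.87 that the article does not give, on a 500/250 split, and on no gain from covariates. Over SD 0.4 to 1.0 the threshold is 11% to 27% of 0.57, so the conclusion does not hang on the exact SD.

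The practical effect falls mainly on small significant increases, where the P<.05 rule and a bound-based rule can point in opposite directions. It would be too strong to say that the test is invalid or that the study is too small.

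**What to change.** Reconcile the aim and the test before the data are analysed, in one of two ways.

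**Option A: keep the no-increase aim.** Use the same analysis of covariance. Report the adjusted difference (vapers minus controls) with its two-sided 95% CI. Conclude no clinically important increase only if the upper limit lies below a prespecified and justified margin smaller than the full 0.57; the plan's more conservative 0.40 is a candidate. State separately whether the interval excludes 0, so that a small but real increase is still reported. Fix the wording for each case:

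- Upper limit below the margin, interval includes 0: no clinically important increase, and no difference shown.
- Interval above 0 but below the margin: an increase, smaller than the margin.
- Upper limit at or above the margin: a clinically important increase is not excluded; say whether the interval also excludes 0.
- Interval wholly below 0: lower scores in vapers.

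**Option B: reword the Introduction's aim as estimation**, in line with the statistics section, and interpret the same interval against the stated threshold.

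Under either option, word the null in terms of adjusted population means. If the full protocol or analysis plan already contains a margin, cite it and align the text.

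Cost: the model, data and sample size are unchanged (step 5). The real cost is that a margin must be justified and fixed after enrollment has finished (November 2023, 748 participants), so the document should record that this was done before analysis. The margin does not remove the limits from self-selection, self-report and cross-sectional design that the Discussion acknowledges.
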